#### Related Power sample

For this co-primary endpoint, there are no consistent epidemiologic data estimating the MDRB prevalence after induction treatment in AML/ HR MDS patients. The power for MDRB eradication based on 20 patients (calculated for the primary endpoint) is as follows:

| Prevalence after AFMT |       | Prevalence before AFMT |       |
|-----------------------|-------|------------------------|-------|
|                       | 0.15  | 0.175                  | 0.2   |
| 0.01                  | 0.557 | 0.649                  | 0.729 |
| 0.02                  | 0.440 | 0.535                  | 0.624 |
| 0.03                  | 0.352 | 0.445                  | 0.535 |
| 0.04                  | 0.284 | 0.370                  | 0.458 |

All documentation of **MaaT Pharma** is PROPRIETARY information and may not be forwarded to third parties without prior written consent from **MaaT Pharma**. Reproductions, either in part or in whole, may not be published or copied in any manner, without the explicit written consent of **MaaT Pharma**

|                                                                                                         |                      |                                                                                               |
|---------------------------------------------------------------------------------------------------------|----------------------|-----------------------------------------------------------------------------------------------|
| [figure not shown]
MaaT Pharma | Protocol             | Protocol N°: MPOH02
EudraCT N° : 2015-004335-12
Version 10.0
Date : 20 November 2017 |
|                                                                                                         | ODYSSEE STUDY |                                                                                               |

0.05

0.230

0.308

0.391

It is apparent that 20 patients do not provide enough power in the assumption where the difference between before and after prevalence is small. A maximum power is expected when the before and after prevalence are 0.2 and .01, respectively.

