## **6. STUDY DESIGN**

### **6.1. Type of study**

Single-arm multicenter prospective interventional trial in hospitalized patients (Phase I/II).

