#### Initial Power sample

By assuming repeated measurement between Sf and the two previous S values, we assume that the correlation R (Sd, Sf) is at least  $R=0.5$ . Without an accurate estimate of the standard deviation of Sd and Sf, we will consider in this first-in-man trial that a change observed as at least half of its standard deviation should be considered as clinically meaningful as defined by Cohen's rules (84). In these conditions, a sample size of at least 30 patients should provide a power of 0.875 to detect a difference of a clinically relevant difference  $\Delta=|Sf-Sd|$ , at a one-tailed significance level of 0.05.

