#### 7.1.2. Evaluation of AFMT efficacy in MDRB eradication

Based on bacterial culture and analysis of resistance gene expression by metagenomics, we will evaluate the prevalence and the quantity of MDRB before (D0), after chemotherapy/antibiotherapy (D29) and after AFMT (D40).

Prevalence of MDRB will be compared between D40 and D29 to evaluate AFMT efficacy in MDRB eradication.

---

All documentation of **MaaT Pharma** is PROPRIETARY information and may not be forwarded to third parties without prior written consent from **MaaT Pharma**. Reproductions, either in part or in whole, may not be published or copied in any manner, without the explicit written consent of **MaaT Pharma**

|                                                                                   |                      |                                                                                               |
|-----------------------------------------------------------------------------------|----------------------|-----------------------------------------------------------------------------------------------|
| [figure not shown] | Protocol             | Protocol N°: MPOH02
EudraCT N° : 2015-004335-12
Version 10.0
Date : 20 November 2017 |
|                                                                                   | ODYSSEE STUDY |                                                                                               |

Further to recruitment difficulties, the company would limit the number of cases. The following table provides the sample size needed for some beta values (from 0.1 until 0.25) and for some effect size (defined as the standardized mean difference). It is apparent that small values of effect sizes need at least 44 patients (for effect size=0.4). However, when the effect size is at least 0.6 and with a beta risk of at least 0.20, 20 patients should constitute an acceptable size.

| Effect Size | Power= | 0.1   | 0.15  | 0.20  | 0.25  |
|-------------|--------|-------|-------|-------|-------|
| 0.4         |        | 66.00 | 57.00 | 49.00 | 44.00 |
| 0.5         |        | 43.00 | 36.00 | 32.00 | 28.00 |
| 0.6         |        | 30.00 | 25.00 | 22.00 | 20.00 |
| 0.7         |        | 22.00 | 19.00 | 16.00 | 15.00 |
| 0.8         |        | 17.00 | 15.00 | 13.00 | 11.00 |
| 0.9         |        | 13.00 | 12.00 | 10.00 | 10.00 |
| 1           |        | 11.00 | 10.00 | 9.00  | 8.00  |

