### Conclusion.

A sample size of 20 patients does not reduce the interest of the study, for the main endpoint (change of dysbiosis), however, the power of the secondary endpoints (including MDRB) will inevitably be reduced. The exploratory feature of this study does allow this relaxed value, and alpha value can be increased (or one-tailed tests should be used) to increase power.

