### 7.3.2. Co-primary endpoint: MDRB eradication

The significance of the difference of prevalence between final (f), deterioration time (d) and baseline time (b) will be assessed a paired t-test. As for the main endpoint, Log transformed values will be used in case the MDRB is distributed according a Log-Normal distribution.

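### The MDRB power table labelled as resting on 20 patients does not follow from 20 patients; at two-sided 0.05 all 15 of its values are too high for that size

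*Protocol*

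**What the plan says.** MDRB eradication is listed as a co-primary objective in section 3 and as a co-primary endpoint in section 7.3.2. Section 6.1 describes a single-arm trial. Section 7.1.2 defines the comparison: "Prevalence of MDRB will be compared between D40 and D29 to evaluate AFMT efficacy in MDRB eradication". Section 7.3.2 fixes the test: the difference in prevalence between the final time, "deterioration time (d) and baseline time (b) will be assessed a paired t-test".

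Under Related Power sample in section 7.1.2, the protocol notes that "there are no consistent epidemiologic data estimating the MDRB prevalence after induction treatment in AML/ HR MDS patients" and then gives the table: "The power for MDRB eradication based on 20 patients (calculated for the primary endpoint) is as follows". Prevalence before AFMT is taken as 0.15, 0.175 or 0.20, and prevalence after it as 0.01 to 0.05. The text below the table adds: "A maximum power is expected when the before and after prevalence are 0.2 and .01, respectively". That cell reads 0.729.

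No formula, alpha or sidedness is given for this table. The only stated level, "at a one-tailed significance level of 0.05", belongs to the diversity endpoint (section 7.1.1, Initial Power sample). The Conclusion of section 7.1.2 remarks that "alpha value can be increased (or one-tailed tests should be used) to increase power", which suggests that the printed MDRB figures are two-tailed but does not say so.

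**The concern.** This table is the only power evidence for a co-primary endpoint, and a reader will take 0.729 as what 20 patients can deliver in the best case. The values cannot be recovered from 20 patients. They coincide with a calculation for a larger number in a different design: two separate groups instead of one group measured twice. If the endpoint is tested two-sided, the real chance of a significant result is lower than stated throughout, and a non-significant result would be weaker evidence against an effect than the table implies.

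**Working it through.** **Inputs.** The prevalences and the 15 powers come from the table in section 7.1.2. The paired structure comes from sections 6.1 and 7.1.2, and the paired t-test from section 7.3.2. The protocol does not give the within-patient association, so two cases are used as assumptions: *no new acquisitions* (every change is a clearance, with rate p1 − p2) and *independent carriage* (clearance rate p1(1 − p2), acquisition rate p2(1 − p1)).

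**1. Can n = 20 give the table?** Pooled and unpooled z, arcsine (one- and two-sample), one-sample z and McNemar approximations were run with n = 20, each at one-sided 0.05, two-sided 0.05 and one-sided 0.10. The closest still misses some cell by 0.059, and none places more than 5 of 15 cells within 0.02.

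**2. What does give it?** A search over n from 8 to 69, with continuity-corrected and paired-t variants added, left one near-exact match, the arcsine formula for two independent groups of n each:

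h = 2·asin(√p1) − 2·asin(√p2); power = Φ(h√(n/2) − 1.96) + Φ(−h√(n/2) − 1.96)

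Best cell (0.20 to 0.01): h = 0.927 − 0.200 = 0.727.
- n = 25: 0.727 × √12.5 = 2.570; Φ(0.610) = 0.729, as printed.
- n = 20: 0.727 × √10 = 2.299; Φ(0.339) = 0.633.

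All cells, for prevalence before AFMT of 0.15 / 0.175 / 0.20:

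| After | Stated | 25 per group | 20 per group |
|---|---|---|---|
| 0.01 | 0.557 / 0.649 / 0.729 | 0.557 / 0.649 / 0.729 | 0.469 / 0.554 / 0.633 |
| 0.02 | 0.440 / 0.535 / 0.624 | 0.440 / 0.535 / 0.624 | 0.366 / 0.449 / 0.530 |
| 0.03 | 0.352 / 0.445 / 0.535 | 0.353 / 0.445 / 0.535 | 0.293 / 0.370 / 0.449 |
| 0.04 | 0.284 / 0.370 / 0.458 | 0.284 / 0.370 / 0.458 | 0.237 / 0.308 / 0.382 |
| 0.05 | 0.230 / 0.308 / 0.391 | 0.230 / 0.308 / 0.391 | 0.193 / 0.256 / 0.325 |

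The largest difference between the stated values and those for 25 per group, before rounding, is 0.0006. Regressing the probit of the stated powers on h gives n = 24.9 per group and a critical value of 1.957.

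**3. Power with 20 pairs.** Every combination of clearances and acquisitions was enumerated from the multinomial distribution. Ranges are over the 15 cells; the best cell is 0.20 to 0.01.

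| Test, alpha 0.05 | No new acquisitions | Independent carriage | Best cell | Cells above stated value |
|---|---|---|---|---|
| Paired t, two-sided | 0.133 to 0.544 | 0.152 to 0.509 | 0.51 to 0.54 | 0 and 0 |
| Exact McNemar, two-sided | 0.011 to 0.164 | 0.029 to 0.169 | 0.16 to 0.17 | 0 and 0 |
| Paired t, one-sided | 0.323 to 0.761 | 0.268 to 0.698 | 0.70 to 0.76 | 14 and 9 |
| Exact McNemar, one-sided | 0.043 to 0.327 | 0.076 to 0.323 | 0.32 to 0.33 | 0 and 0 |

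The spread comes from how few changes each test needs. With no acquisitions, the paired t-test on 20 pairs rejects from 3 clearances one-sided (t = 1.83 against 1.73) and from 4 two-sided (t = 2.18 against 2.09). Exact McNemar needs 5 (p = 1/32) and 6 (p = 2/64). In the best cell the clearances are then binomial(20, 0.19), and the probabilities of at least 3, 4, 5 and 6 are 0.761, 0.544, 0.327 and 0.164.

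**The case against.** **The origin of the table is inferred.** The protocol never mentions 25, and the match is not unique. If a paired version of the arcsine formula uses √(n / (2(1 − ρ))), then 20 pairs with ρ = 0.2 give 20/1.6 = 12.5, the same factor as 25/2. This stands: the documents do not establish how the table was made. It does not rescue the table, because no such correlation is stated. In the best cell ρ = 0.2 is also practically the largest value possible, √(0.01 × 0.80 / (0.20 × 0.99)) = 0.201, reached with no new acquisitions. There the planned paired t-test has two-sided power of 0.54, not 0.729.

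**One-sided testing.** A reader might infer that every stated power is too high whatever the level. The documents do not support that. At one-sided 0.05, the only level the protocol states anywhere, the planned paired t-test exceeds the table in 9 to 14 of 15 cells, and the arcsine formula with 20 per group exceeds it in all 15 (0.743 in the best cell). The claim holds only at two-sided 0.05.

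**Choice of test.** A reader might also infer that the design cannot reach half of 0.729. That is true only if exact McNemar replaces the paired t-test of section 7.3.2. A single comparison, 3 clearances against none (exact one-sided p = 0.125), might suggest that the t-test breaks its level. Enumeration with equal prevalences of 0.05 to 0.20 and independent carriage gives it a one-sided size of 0.028 to 0.051, so that is not borne out there; exact McNemar has 0.001 to 0.017 and is very conservative.

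**Low power is already admitted.** Section 7.1.2 says that 20 patients are too few when the prevalence difference is small, and its Conclusion accepts reduced power for MDRB and calls the study exploratory. The sample size of 20 comes from the effect-size table, not from this one. All of this lowers the severity, but a general caveat does not correct 15 printed figures.

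**Conclusion.** The point holds in limited form. The 15 powers attributed to 20 patients are not reproducible from 20 patients by any standard method tried, and they agree within 0.001 with two independent groups of 25 at two-sided 0.05, a structure that this trial does not have.

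At two-sided 0.05 all 15 are overstated for n = 20. In the best cell, 0.729 becomes 0.633 by the same formula with 20 per group and 0.51 to 0.54 for 20 pairs with the planned test. The paired figures rest on the protocol's own prevalences and on the two assumed discordance patterns. At one-sided 0.05 the direction of the error depends on the test. The protocol's conclusion that power for MDRB is limited is unaffected. This is a should-fix.

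**What to change.** Recompute the table for 20 pairs under the test actually planned, and name that test, alpha and sidedness beside it. Show each cell as a range from no new acquisitions to independent carriage, because neither assumption has data behind it. Restate the best-case sentence to match: with the paired t-test of section 7.3.2, power at 0.20 versus 0.01 is 0.51 to 0.54 two-sided or 0.70 to 0.76 one-sided. If a different test is adopted, the table should follow that test; exact McNemar would give 0.16 to 0.17 two-sided or 0.32 to 0.33 one-sided in the same cell.

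The cost is one table and one or two sentences, with no extra patients or measurements. If testing is two-sided, the stated figures become less favourable. If one-sided testing is intended, it has to be declared for this endpoint.

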### Conclusion.

A sample size of 20 patients does not reduce the interest of the study, for the main endpoint (change of dysbiosis), however, the power of the secondary endpoints (including MDRB) will inevitably be reduced. The exploratory feature of this study does allow this relaxed value, and alpha value can be increased (or one-tailed tests should be used) to increase power.

## **7.2. Secondary endpoints**

### **7.2.1. Definition of a dysbiosis signature**

The current knowledge of dysbiosis measurement remains very limited, so far. The main measurement is based on diversity itself measured by Simpson Index, which constitutes today the most usual measure, although probably limited to a particular aspect of the microbiota dispersion. Other parameters of diversity exist (in particular, the Shannon Index), but other aspects of the microbiota will be investigated. A first generalization of diversity will be co-abundance, defined as the probability of co-existence of two species. This calculation generalizes the diversity index, restrained to the co-existence of the same species. Another generalization is the Utility function associated with each species and characterized by either a linear utility or a utility area (included between two thresholds). In particular, the calculation of these parameters becomes complex when the number of species increases, thus one of the important objectives of the statistical analysis based on these data will be to determine the optimal level of species hierarchy Tree, allowing a sufficient precision. These endpoints, which are exploratory, will be defined with accuracy in the Statistical Analysis Plan (SAP). In what follows, we call them Alternative Dysbiosis (AD) measurements

|                                                                                                         |                      |                                                                                               |
|---------------------------------------------------------------------------------------------------------|----------------------|-----------------------------------------------------------------------------------------------|
| [figure not shown]
MaaT Pharma | Protocol             | Protocol N°: MPOH02
EudraCT N° : 2015-004335-12
Version 10.0
Date : 20 November 2017 |
|                                                                                                         | ODYSSEE STUDY |                                                                                               |

### **7.2.2. Effect of dysbiosis correction on patient clinical status**

Previous researches provided some evidence of the association between the observed disorder or disturbance of the normal microbiota and the patient health status, infectious and digestive status. In the following, we call these variables Health Status Related HSR variables. In particular, one of them is the MDRB measured at each visit of the trial. For simplification of description of the following development, we keep the general term HSR to represent any health-status related variable measured, although the MDRB reduction will constitute the most important endpoint among any possible HSR.

### **7.2.3. Safety variables**

#### **7.2.3.1. Adverse events**

Each AE will be coded to a “preferred term” and associated “primary system-organ class” according to an established and validated adverse reaction dictionary (MedDRA) before the treatment code is broken. The AE endpoint will be the number of subjects experiencing at least one event, regardless of relationship of the event to the study drug.

Adverse events will be categorized into three categories:

- The treatment emergent adverse event (TEAE),
- The pre-AFMT adverse event,
- The post-AFMT adverse event.

Definitions are given below.

Treatment-Emergent Adverse Events (TEAEs) will be defined as events occurring on or after the first study drug intake. Additionally, events present before the first study drug intake, but worsening or becoming serious under treatment will be considered as TEAEs. Although every effort will be made to establish the onset date and time, events with missing onset date will be considered as TEAEs.

Events occurring, worsening or becoming serious before the first study drug intake will be considered as pre-AFMT adverse events and events occurring, worsening or becoming serious 1 day or more after the last study AFMT will be considered as post-treatment adverse events.

|                                                                                   |                      |                                                                                               |
|-----------------------------------------------------------------------------------|----------------------|-----------------------------------------------------------------------------------------------|
| [figure not shown] | Protocol             | Protocol N°: MPOH02
EudraCT N° : 2015-004335-12
Version 10.0
Date : 20 November 2017 |
|                                                                                   | ODYSSEE STUDY |                                                                                               |

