### ***D30 and D31 (between D25 and D36 depending on patient's condition) - Fecal transplantation***

The AFMT will be performed 24 hours after antibiotics discontinuation and after aplasia completion. The patient will receive 2 inocula of 150 mL corresponding to a total of 60g (2 x 30g) of faeces, according to the procedure (**Appendix 1**). A rectal preparation for AFMT will include 2 enemas with "Normacol lavement" the night before and the morning of the procedure, enhancing the potential for FMT to provide a "fresh start" in repopulating the colonic habitat of the patient. Indeed, the lavage will enhance FMT success by flushing out residual faeces, antibiotics, and *C. difficile* bacteria, toxins and spores (83). The rectal preparation and AFMT will not be performed in case of persistent mucositis, colitis, or haemorrhoids, that constitute exclusion criteria. A third inoculum is available in case of technical incident (rejection of the inoculum by the patient within 1 hour after transplantation). Fecal transplantation is performed by a rectal probe introduced in the patient's rectum. A tubing, ending with a rectal probe, is directly connected to allow the inoculum to reach the colon. The patient will remain in lying position for 1 hour to ensure a good transplantation and avoid any loss. Patient's vital signs (blood pressure, pulse, temperature, respiratory rate) will be monitored during all the time of the transplantation process, until the expulsion of the remaining transplant but at least 2 hours after AFMT. Monitoring will also focus on the recovery of intestinal transit, onset of abdominal pain, occurrence of fever before the patient's hospital discharge. In case of severe adverse event, the hospitalization will be extended to treat the event. In case of procedure-related SAE or SADR (Serious Adverse Drug Reaction) during the first AFMT, the second AFMT will not be done. Post-transplant clinical tolerance will be monitored with a questionnaire (**Appendix 1**) and the logbook (**Appendix 2**).

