Medical and scientific judgment should be exercised in deciding whether expedited reporting is appropriate in other situations, such as important medical events that may not be immediately life-threatening or result in death or hospitalization but may jeopardize the subject or may require intervention to prevent one of the other outcomes listed in the definition above.

- New development

Any new safety data:

- which could significantly alter the benefice/risk balance evaluation of the advanced therapy product or the study
- or which could lead to consider modifications regarding the advanced therapy or the conduct of the study

For examples:

- A SAE that could be linked to the investigation and diagnostic procedures of the study and that could change the course of this study
- A significant risk for the study population (e.g. lack of efficiency of the investigational medicinal product used in the treatment of a life-threatening disease)
- Significant results from animal studies recently completed

|                                                                                                         |                      |                                                                                               |
|---------------------------------------------------------------------------------------------------------|----------------------|-----------------------------------------------------------------------------------------------|
| [figure not shown]
MaaT Pharma | Protocol             | Protocol N°: MPOH02
EudraCT N° : 2015-004335-12
Version 10.0
Date : 20 November 2017 |
|                                                                                                         | ODYSSEE STUDY |                                                                                               |

- Early discontinuation or temporary interruption for safety reasons of a clinical trial conducted in another country with the same investigational medicinal product
- An unexpected SAE to a non-investigational medicinal product required to conduct the study (e.g. challenge agents, emergency treatment)

The AE intensity is evaluated by the investigator according to the following classification:

- **Mild:** Awareness of signs or symptoms, but easily tolerated and are of minor irritant type causing no loss of time from normal activities. Symptoms do not require therapy or a medical evaluation; signs and symptoms are transient.

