### Date et heure de dernière prise des antibiotiques:

le \_\_/\_\_/\_\_ à \_\_ h \_\_

Faire un lavement avec Normacol au patient.

A quelle heure le lavement a-t-il été effectué? à \_\_ h \_\_

Le lendemain, 2 heures avant la transplantation, faire un lavement avec Normacol au patient.

A quelle heure le lavement a-t-il été effectué? à \_\_ h \_\_

Attendre l'évacuation des selles.

Le patient a-t-il évacué les selles? Oui ☐ Non ☐

Procéder à la transplantation (page 2).

|                                                                                   |                      |                                                                                            |
|-----------------------------------------------------------------------------------|----------------------|--------------------------------------------------------------------------------------------|
| [figure not shown] | Appendix 1           | Protocol N°: MPOH02
EudraCT N° : 2015-004335-12
Version .1 9.0
Date : 28 Feb 2017 |
|                                                                                   | Etude ODYSSEE |                                                                                            |

Heure de fin de la transplantation : \_\_\_\_\_ h \_\_\_\_\_

Totalité de l'inoculum injectée : Oui ☐ Non ☐

Si non, préciser pourquoi :

-----

-----

-----

Le patient a-t-il évacué l'inoculum Oui ☐ Non ☐

Si oui, préciser l'heure : \_\_\_\_\_ h \_\_\_\_\_

Indiquer, si possible, le volume approximatif de perte \_\_\_\_\_ mL

|                                                                                   |                      |                                                                                            |
|-----------------------------------------------------------------------------------|----------------------|--------------------------------------------------------------------------------------------|
| [figure not shown] | Appendix 1           | Protocol N°: MPOH02
EudraCT N° : 2015-004335-12
Version .1 9.0
Date : 28 Feb 2017 |
|                                                                                   | Etude ODYSSEE |                                                                                            |

|                                                                        |
|------------------------------------------------------------------------|

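### Events between the first preparation enema and the first inoculum are classed as pre-AFMT and pooled with induction-chemotherapy events; they need a category of their own

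*Protocol*

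**What the plan says.** Protocol Section 7.2.3.1 sorts adverse events into three categories: treatment-emergent, pre-AFMT and post-AFMT. The first begins at the product: "Treatment-Emergent Adverse Events (TEAEs) will be defined as events occurring on or after the first study drug intake". The second takes what comes earlier: "Events occurring, worsening or becoming serious before the first study drug intake will be considered as pre-AFMT adverse events". Two exceptions pull earlier or undated events into the first category: "events present before the first study drug intake, but worsening or becoming serious under treatment will be considered as TEAEs", and "events with missing onset date will be considered as TEAEs".

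Section 6.4.2 (fecal transplantation, D30 and D31) requires bowel preparation: "A rectal preparation for AFMT will include 2 enemas with" a named product, given "the night before and the morning of the procedure". Appendix 1, the form for carrying out and evaluating the transplantation, puts the first enema on the evening that antibiotics stop. It puts the second on the next day: "Le lendemain, 2 heures avant la transplantation, faire un lavement avec Normacol au patient". The form has a field for the time of each.

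**The concern.** The preparation is given only because the patient is about to receive AFMT, so any harm it causes comes with the trial's intervention. Yet the category rule separates it from the inoculum and files it with the events of induction chemotherapy and aplasia. Abdominal pain, bleeding or fever that starts after an enema and resolves before the inoculum, or simply does not get worse after it, would read as one more chemotherapy-period event.

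The title presents a feasibility and safety study. Section 3 lists the safety of AFMT and the feasibility of the AFMT procedure as objectives. A reader of the treatment-emergent and post-AFMT results would see the inoculum's acute tolerance but not that of the step needed to deliver it. The direction is one-sided: preparation harm can only be missing from those two categories.

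**Working it through.** The plan states no figure on this point, so the check sets the timing against the categories.

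**Timeline.** The study product is the inoculum, so first study drug intake means the first inoculum. Both preparation enemas for the first AFMT precede it (Section 6.4.2, Appendix 1).

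**Classification under Section 7.2.3.1.**

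| Event | Category |
|---|---|
| Starts after the evening enema, resolves before the inoculum | Pre-AFMT |
| Starts after an enema, becomes serious before the inoculum, no worse afterwards | Pre-AFMT |
| Starts after an enema, persists unchanged after the inoculum | Pre-AFMT |
| Starts after an enema, worsens or becomes serious after the inoculum | TEAE |
| Onset date missing | TEAE |
| Starts after the first inoculum, including around the second AFMT | TEAE |

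The first three rows are the exposed cases.

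**Share of the pre-AFMT period.** The interval from evening enema to first inoculum is not stated in hours; I assume 12 to 24 h. The transplantation window is D25 to D36 for two consecutive days, so the first inoculum falls between D25 and D35.

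- Smallest share: 0.5 day / 35 days = 1.4%.
- Nominal D30 with 24 h: 1 / 30 = 3.3%.
- Largest share: 1 / 25 = 4.0%.

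The category label alone therefore cannot single out preparation events from the other 96% to 98.6% of the period.

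**Whether other outputs would show them.**

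- Section 9.1.2.3.1 records all adverse events from consent, so the data exist.
- The endpoint in Section 7.2.3.1 counts subjects with at least one event of any kind. It includes these events but cannot isolate them. For scale, Supplementary Table 5 sums to 415 events in 25 patients after the first 24 hours (415 / 25 = 16.6 per patient), so this count is probably close to its ceiling.
- Supplementary Table 4 covers the 24 hours after AFMT and so excludes the preparation.
- Supplementary Figure 5 reports by visit interval. V2 to V3 spans the preparation but runs nominally from D29 to D40, or 11 days.
- Section 4.5 refers to a transplantation period without defining it, so it does not override the categories.

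**The case against.** The strongest objection is that nothing is lost. Pre-AFMT is a reported category, all events are recorded, the endpoint is not restricted to TEAEs, and the serious-event report form asks for causality against study procedures. This stands: a reader might infer that preparation harms drop out of the safety result altogether, and the protocol does not say so.

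Second, starting TEAEs at first intake of the investigational product is ordinary practice. Section 6.4.2 also names the rectal preparation and AFMT as two steps, so the view that AFMT begins the evening before is a reading of Appendix 1, not a stated definition. This too stands, and it is a reason to leave the TEAE start alone. Section 9.1.1 lists "An unexpected SAE to a non-investigational medicinal product required to conduct the study" among new safety developments. That shows such harm is relevant to the study, but it is a reporting provision and sets no analysis window.

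Third, a reader might infer that a patient whose AFMT is cancelled because of the preparation disappears from the safety denominator. Such a patient would have no TEAE, but the protocol fixes no treated-only denominator; that restriction appears in the supplementary results tables. Supplementary Table 9 counts 5 of 37 screen failures with FMT not performed because of the patient's condition, and nothing links these to the enemas.

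Fourth, it is tempting to scale from Supplementary Table 4: 5 events / 25 patients = 0.2 per patient-day, and 0.2 x 25 patients x 0.5 to 1 day = 2.5 to 5 misplaced events. If that table pools both AFMTs, exposure is 50 patient-days and the result halves to 1.25 to 2.5. Either way it assumes that the enema causes events at the rate seen after the inoculum, which no passage supports.

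What the objections leave untouched is the category rule itself, which is written into the protocol and mixes a trial-required step with chemotherapy events.

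**Conclusion.** The point holds as misclassification and dilution. Harm from the preparation that starts before the first inoculum and does not later worsen or become serious falls outside both the treatment-emergent and post-AFMT categories, and is pooled with 25 to 35 days of induction-phase events. The exposed window is 12 to 24 hours, before the first AFMT only. That length is an assumption; the share of 1.4% to 4.0% follows from it and from the D25 to D35 range. The count of affected events cannot be derived from the documents and may be zero. The TEAE anchor is not wrong in itself. What is missing is a category that makes a trial-imposed step visible in a trial with AFMT safety and procedure feasibility among its objectives. It is a modest issue, worth correcting because the correction is nearly free.

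**What to change.** Keep TEAEs from the first inoculum. Add to Section 7.2.3.1 a separate AFMT-preparation category: events with onset, worsening or becoming serious from the first preparation enema to the first inoculum. Report it on its own line beside the TEAEs. The denominator should be all patients who received at least one preparation enema, including any not then inoculated. An event that begins in this window and worsens after the inoculum remains a TEAE as now; a footnote should say that it also appears on the preparation line, so that the two are not added together.

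The cost is a few sentences in Section 7.2.3.1 and the matching SAP output. Enema times are already on the Appendix 1 form, and Section 7.2.3.1 already seeks onset date and time. Two practical points follow. Events on the day of the inoculum need an onset time to be placed. And because the form is addressed to the person who performed the transplantation, it should also be completed when a prepared patient is not inoculated. The downside is small: some background end-of-aplasia events will appear on the new line, where they can be seen for what they are without entering the TEAE count.
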